### 3.1.2 Internal validity

Power calculations indicate that the selected number of health zones will be sufficient to detect the expected impact on our primary outcomes. After randomization, the soundness of the randomization as a procedure to control for confounding will be checked by comparing variables obtained through the baseline survey and through community level data. Examples of baseline variables that will be compared are maternal age, education and occupation; child age and gender; birth weight of the child; duration of breastfeeding length; and initial vaccination status. We will also include community level baseline variables such as distance to health center and District Medical Office, road access and presence of community health workers. Although blinding of treatment will not be possible due to the very nature of the intervention, we do not expect Hawthorne effects to be significant in this case due to the length of the program. We also do not foresee important concerns due to differential attrition in the two arms because of the long-standing relationship of ZCAHRD in all of these communities (both the control and intervention) established through the previous ZamCAT study.

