## Sample Size Calculations

The study is designed to detect increases in standardized child development scores of 0.5 standard deviations with power = 0.9. The main assumptions underlying this calculation are an average group size of 20 children in each of the 30 zones, and an intra-class correlation coefficient of 0.1 (a design effect of 2.9). Similarly, the study is powered to detect an increase in height-for-age z-scores of 0.5 standard deviations in the intervention arm relative to the control arm. We aim to enroll 250 children in each study arm for a total sample of 500 children. In order to account for lost to follow-up, we aim to recruit up to 5% additional children per study arm (262 per arm).

For the year two follow-up assessment, we are powered to detect an increase in standardized child development scores, as measured by the BSID-III, of 0.3 standard deviations with power 0.8.

Sample size for health facility surveys and feeding centers is seven. There will be 10 health workers interviewed (assuming 2 per health facility), 5 national, provincial and district level nutritionists or clinical-care specialists and the feeding sample size for assessment of dietary intake will be all willing and enrolled intervention children (estimate 275).

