# Data analysis

We will use the following primary outcomes:

1. Proportion of children with stunting (height-for-age Z-score less than 2 standard deviations below the mean);
2. Child development scores using the INTERGROWTH tool;

Other outcomes of interest include:

1. Proportion of children receiving all age-appropriate vaccines
2. Proportion of children receiving vitamin A supplementation;
3. Number of well-baby visits attended;
4. HOME score;
5. Average time spent reading with the child;
6. Average time spent playing with the child;
7. Proportion of women scoring as depressed, based on the SRQ-20.

We will investigate the relative risk associated with random group assignment as a fixed covariate predicting each outcome using generalized estimating equations (GEE) models that take into account the clustering by health facility. We will use an exchangeable correlation structure in the model.

We will compare baseline characteristics between the two groups that may be related to the outcome, but we expect randomization to have created reasonably balanced groups. Categorical variables will be compared between groups using the chi-square test or Fisher’s exact test if cell sizes are small, continuous variables using t-tests if normally distributed or non-parametric Wilcoxon rank sum tests, if non-normal. We will adjust for confounders as appropriate.

Potential confounders include: maternal education, paternal education, socio-economic status, baseline nutritional status, and presence of food insecurity. The process of randomization should help to balance confounders across the two study arms. Crude and adjusted risk ratios will be presented with 95% confidence intervals in appropriate tables.

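### Risk ratios are set as the effect measure for every outcome although five of the nine are not proportions, and baseline balance is tested as if children were independent

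*Protocol*

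**What the plan says.** **Effect measure.** The protocol's Data analysis section lists two primary and seven other outcomes. It then says "We will investigate the relative risk associated with random group assignment as a fixed covariate predicting each outcome", using GEE with an exchangeable correlation structure, and on reporting: "Crude and adjusted risk ratios will be presented with 95% confidence intervals in appropriate tables". It names no other effect measure. The Sample Size Calculations section works on a different scale: "The study is designed to detect increases in standardized child development scores of 0.5 standard deviations with power = 0.9".

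**Baseline comparison.** Data analysis says "Categorical variables will be compared between groups using the chi-square test", or Fisher's exact test for small cells, and gives t-tests or Wilcoxon rank sum tests for continuous variables. It mentions no allowance for clustering. Section 3.1.2 (Internal validity) says "Examples of baseline variables that will be compared are maternal age, education and occupation; child age and gender", then adds further child-level variables and some community-level ones.

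**Adjustment.** Directly after the tests comes "We will adjust for confounders as appropriate". The list that follows gives parental education, socio-economic status, nutritional status at baseline and food insecurity, all as possible confounders. Child age and sex are in the balance check of section 3.1.2 but not in this list.

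**Design.** Under Determination of clusters and randomization, zones are randomised half and half within each of five facilities (15 against 15), with strata based on zone population and distance to the facility. The sample size assumes "an average group size of 20 children in each of the 30 zones", with an ICC of 0.1 and a design effect of 2.9.

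**The concern.** A protocol should say on what scale each primary comparison will be made. Here the stated scale suits stunting but not the development score. An analyst who follows the text must either depart from it or dichotomise the score at a cut-off that the protocol does not define. The design difference of 0.5 SD could then not be compared directly with the reported result.

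The baseline tests contradict the design in another way. Children in the same zone resemble each other, and zones are what was randomised. A test that counts children as independent understates the standard error of the difference between arms, so it reports imbalance more often than its nominal level. Because an open adjustment rule comes next, such false alarms could shape the adjusted analysis.

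**Working it through.** **1. Outcome types set against the stated measure**

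| Outcome (Data analysis) | Type | Risk ratio fits? |
|---|---|---|
| Stunting (primary) | proportion | yes |
| Development score (primary) | score | no |
| Age-appropriate vaccines | proportion | yes |
| Vitamin A | proportion | yes |
| Well-baby visits | count | no |
| HOME score | score | no |
| Reading time | continuous | no |
| Playing time | continuous | no |
| Depressed on the SRQ-20 | proportion | yes |

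Four of nine fit and five do not, one of them a primary outcome.

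**2. The protocol's own sample size**

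The inputs are 20 children per zone, ICC 0.1, a difference of 0.5 SD and power 0.9. Two-sided 5% is assumed, in line with the 95% intervals.

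- Design effect = 1 + (20 − 1) × 0.1 = 2.9, as stated.
- Children per arm without clustering = 2 × (1.96 + 1.2816)² / 0.5² = 84.1, rounded up to 85.
- With clustering: 85 × 2.9 = 246.5, against 250 stated. With 250 per arm the power is 0.907.

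The calculation reproduces, so the protocol plans for clustering here and leaves it out of the baseline tests.

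**3. False-alarm rate of a test that ignores clustering**

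The rate for a nominal 5% test is 2 × [1 − Φ(1.96 / √DEFF)], with DEFF = 1 + (m − 1) × ICC. At the enrolment target, m = 500 / 30 = 16.7. The protocol gives no ICC for baseline variables, so the ICC is an assumption and is varied.

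| Assumed ICC | DEFF at m = 16.7 | False-alarm rate |
|---|---|---|
| 0.01 | 1.157 | 6.8% |
| 0.02 | 1.313 | 8.7% |
| 0.05 | 1.783 | 14.2% |
| 0.10 | 2.567 | 22.1% |
| 0.15 | 3.350 | 28.4% |

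For ICC 0.10: 1.96 / √2.567 = 1.223, which gives 22.1%. With the protocol's design effect of 2.9: 1.96 / √2.9 = 1.151, which gives 25.0%.

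**4. Simulation check**

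The simulation used five facilities with six zones each, three zones per arm within each facility, and 500 children in all.

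- t-test, all of an ICC of 0.1 between zones within facilities: 22.8%.
- t-test, ICC 0.05: 14.2%. ICC 0.02: 8.9%.
- t-test, half of an ICC of 0.1 between facilities, which randomising within facility balances: 13.2%.
- Chi-square test of a 36% characteristic, obtained by cutting a normal variable with ICC 0.1: 16.9%.

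All are above 5%.

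**The case against.** **The covariate model belongs in the SAP.** This largely stands. The SAP is not at hand, and a protocol may leave the exact list to it. Nutritional status at baseline is already named as a candidate, so it would be wrong to call baseline HAZ absent. What remains is that the protocol itself places an open rule straight after tests that are not valid for the design.

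**The link from tests to adjustment is inferred.** This also stands. A reader might infer that significant baseline tests will select the covariates. The order of the sentences allows that, but no such rule is written, and crude results will be shown beside adjusted ones.

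**The 22% borrows the outcome ICC.** Correct. It is a conditional figure. Some baseline variables, child sex for example, may hardly cluster, and randomising within facility removes part of the variation between zones. A reader might also expect worse results for community-level variables such as distance. But section 3.1.2 does not say that these are tested child by child, and distance is a stratification factor.

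**A ratio can be computed for a score.** True: a log-link GEE gives a ratio of means for a positive score and a rate ratio for a count. A reader might infer that the development score has no computable effect measure, and that goes too far. But a ratio of means is not a risk ratio, the protocol does not name it, and it does not correspond to a difference in SD units.

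**A large precision gain is being lost.** A reader might infer this for both primary outcomes, but the documents do not support it. Under Data capture/paper storage, neurocognitive assessment is at endline only, so the development score has no baseline value. Stunting is binary, and no correlation between baseline and endline HAZ is given.

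**Conclusion.** Two faults hold. The firmer is the effect measure: a relative risk for every outcome is wrong as written for five of nine, including a primary outcome that the protocol powers in SD units. This rests on the text alone.

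The second is that the baseline tests ignore the randomised unit. Their false-alarm rate is about 22% if baseline variables share the protocol's outcome ICC of 0.1 (25% at its design effect of 2.9). It is about 7% to 28% over assumed ICCs of 0.01 to 0.15, and about 13% if half of an ICC of 0.1 lies between facilities. The direction is certain for any variable that clusters by zone within facilities; the size depends on ICCs that the protocol does not give. The adjustment rule leaves room for these tests to steer the model, but the protocol does not say that they will. This should be corrected, but it does not undermine the design.

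**What to change.** - **Effect measures.** Replace the single relative-risk sentence with measures by outcome type: risk ratios for stunting, vaccination, vitamin A and depression; mean differences (identity link) for the HOME score, reading time, playing time and the development score, with the last in SD units; and a rate ratio for well-baby visits. Apply the same to the BSID-III score at the year two follow-up, which is powered at 0.3 SD and has no effect measure of its own under Objective 10.
- **Baseline balance.** Delete the significance tests. Describe each variable by arm, and state that baseline tests will not select covariates.
- **Adjustment.** Name the covariates in advance, in the protocol or by reference to the SAP: the randomisation strata (facility, zone population and distance), baseline HAZ for stunting, and child age and sex for the development score. Age matters because children enrol at 6 to 12 months and are assessed twelve months later, so they span about 18 to 24 months at endline.

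The cost is wording only. Height is measured at baseline, child age and sex are among the variables that section 3.1.2 compares, and the strata are known from the randomisation.

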**Analysis of objectives 5-7**

Hand written notes will be taken by the interviewer in addition to an audio recording of the interview. The notes will then be coded for common themes and outliers. For analysis of KII data, we will focus on individual views and will, where relevant, look at the proportion of total respondents who report particular views. To the greatest degree possible, this analysis will begin during data collection or shortly after the KIIs are completed in order to permit participation in the analysis by the interviewers who conducted the KIIs and therefore who will be most familiar with the information collected.

At the beginning of the study, a one time, one-day dietary intake will be collected by each CDA prompting the mother or caregiver to complete a 24-hour food recall of their child’s food and drink intake as described in the GAIN working Paper Series. (43) Descriptive frequencies of food intake and proportions of food groups represented will be examined and comparative analysis to WHO guidelines will be performed.

**Analysis of objectives 8: perceptions and behavioral change on mother groups**

Data analysis for focus groups: Focus group discussions will be transcribed and analyzed using NVIVO or similar qualitative analysis software. Emerging common themes and channels will be highlighted. Quotes (without names made, nor facility mentioned) will possibly be included in the manuscript.

**Analysis for Objective 9:**

The parenting assessment will provide information on how parenting behaviors have changed since the last assessment in October 2015. We will primarily look at the number of activities that parents indicate completing with the child.

**Analysis for Objective 10:**

At the year two follow-up, we will measure the following primary outcomes:

1. Proportion of children with stunting (height-for-age Z-score less than 2 standard deviations below the mean);
2. Child development scores using the BSID-III;

Other outcomes of interest include:

- 1. Child diet diversity
  2. Caregiver-child interactions
  3. Proportion of caregivers scoring as depressed, based on the SRQ-20.

# Funding & Budget

The study is funded through the *Grand Challenges Canada’s Saving Brains: Scaling Impact* project. Total project budget is Canadian $ 250,000.

The extension for mother groups and the follow-up assessment is funded through the DFID Policy Research Grant for a budget of approximately US$ 163,000.

# Time Frame

| Development of intervention materials and BU IRB/Zambian ethics committee approvals | Sept 2013 – April 2014 |
| --- | --- |
| Surveyor and CDA recruitment and training | April 2014 |
| Pre-testing data collection instruments, enrollment and baseline survey | May 2014 |
| Intervention rollout | September 2014 |
| Endline evaluation | October 2015 |
| Data analysis | November 2015 |
| Year 1 report and data dissemination | December 2015 |
| Parenting assessment | April 2016 |
| Mothers group extension | April 2016 |
| Year 2 (follow-up) evaluation | November 2016 |

